### Procedure for unblinding of needed {17b}

Not applicable since there is no blinding planned.

## Data collection and management

### Plans for assessment and collection of outcomes {18a}

The researchers of the study group will conduct the questionnaires and be responsible for data collection. The questionnaires, scores and indices (SUS, NASA TLX, Charlson Comorbidity Index and Dindo-Clavien Scores) used in this trial have been used and validated in prior studies [17–20]. Furthermore, senior surgeons and residents will be interviewed regarding their teaching respectively learning experience. Data will be collected in a local database using SPSS Statistics Version 27 (IBM, NY, USA).

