### Intervention description {11a}

After written consent, the patients are randomized into one of four groups using an envelope system. Randomization is not conducted by the researchers but by an impartial study nurse. Reconstruction of the preoperative CT scan into a 3D data set is performed by the researchers of the study group in the program Synapse 3D (Fujifilm Europe GmbH, Düsseldorf). In case of randomization into the 3D print group, the data set is anonymized and STL files are sent to a cooperating company (Cella Medical Solutions, Murcia, Spain) for printing. According to randomization, the 3D data set is then displayed to the surgeon assigned to the case not later than the day before surgery for resection planning. The surgeon is assisted by a member of the study group in terms of technical support and calculation of the planned resection volume (RLV1). At the end of surgery, the actual resection volume (RLV2) is determined by water displacement volumetry. A questionnaire about usability and subjective task load using the System Usability Scale (SUS) [19] and NASA Task Load Index (TLX) [20] is presented to the surgeons after operation. The data will be collected in a local database, to which only researchers of the study group have access. Data will be stored for 10 years according to the requirements of the local ethics committee.

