### Strategies to improve adherence to interventions {11c}

Adherence to intervention will be boosted by the technical support by the research group. Especially for surgeons, who have not used a VR head-mounted display before, help and guidance are necessary in the beginning. It is to be expected that the support needed will decrease during the course of the study.

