### Outcomes {12}

Primary outcome is the quotient of planned resection volume (RLV1) and actual resection volume (RLV2) calculated as (RLV2-RLV1)/RLV1. The resection volume will be measured in millilitres; planned resection volume will be measured using one of the four demonstration modes and volumetry no late than the day before surgery. Actual resection volume will be measured the day of surgery. This parameter is critical to determine how accurate the predicted resection volume is between the different groups.

Secondary outcome consists of usability and subjective task load using SUS and the NASA TLX. A system is less likely to be used, if it is complicated or the controls are hard to remember or challenging to conduct. Thus these scores will show if implementation into daily clinical use is feasible for the different demonstration modes. The described systems are being tested in order to simplify liver resection planning and teaching, thus these measures are critical to determine usability and likelihood of daily use.

Furthermore, patients’ characteristics as well as intraoperative outcome (i.e. resection margin, blood loss, duration of surgery), pathological findings and postoperative morbidity and mortality are assessed in order to describe the study collective properly. Since liver resections can vary greatly in extent even in the chosen group of major resections, it is important to put patients’ characteristics and intraoperative and postoperative measures into perspective with the planned and actual surgical procedure.

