## Oversight and monitoring

### Composition of the coordinating centre and trial steering committee {5d}

The trial steering committee will be composed of one principal investigator and two main investigators, in charge of administration and supervision of the study. Three physicians, who are part of the research group, will be responsible for conducting the trial in the coordinating centre, as well as data management. One study nurse will assist in the trial.

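### SUS and NASA TLX are conducted by the study group that also builds the 3D models and supports the surgeon, which leaves the usability ratings open to courtesy bias.

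*Protocol article*

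**What the plan says.** All references are to the protocol article.

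- **Who conducts the questionnaires.** Section {18a}: "The researchers of the study group will conduct the questionnaires and be responsible for data collection".
- **Who builds the models.** Section {11a}: "Reconstruction of the preoperative CT scan into a 3D data set is performed by the researchers of the study group".
- **Who helps with planning.** Section {11a}: "The surgeon is assisted by a member of the study group in terms of technical support and calculation of the planned resection volume".
- **What that help is for.** Section {11c}: "Adherence to intervention will be boosted by the technical support by the research group". It then singles out one mode: "Especially for surgeons, who have not used a VR head-mounted display before, help and guidance are necessary in the beginning".
- **How large the team is.** Section {5d}: "Three physicians, who are part of the research group, will be responsible for conducting the trial in the coordinating centre, as well as data management".
- **What the scores are used for.** Section {12} names usability (SUS) and subjective task load (NASA TLX) as the secondary outcome and concludes: "Thus these scores will show if implementation into daily clinical use is feasible for the different demonstration modes".

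Section {17a} plans no blinding, and section {9} places the trial in a single department. Section {11a} has the questionnaire given to surgeons after the operation, and section {19} keeps questionnaires on paper within the research team, which also enters and checks the data. No independent administrator and no sealed or anonymous return is described.

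**The concern.** SUS and NASA TLX record what the surgeon is willing to say about the mode just used. Here the people who collect the answer belong to the group that prepared the model and helped the surgeon use it, and they work on a trial in the surgeon's own department. Respondents in that position tend to be polite about the work of the person asking.

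If the politeness were equal in all four arms, it would cancel in the comparisons. It may not be equal. Routine CT viewing is the existing standard, whereas the 3D presentations are what the group brings to the trial, and section {11c} foresees extra help for VR. A reporting shift that differs by arm is added to any true difference in usability, and no analysis of the collected scores can separate the two. At stake is the statement in section {12} that the scores will show whether daily use is feasible, and the use in section {6a} of the results to decide whether the techniques are applied routinely.

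**Working it through.** **Step 1: is the overlap in the text?** Sections {11a}, {11c} and {18a}, side by side, assign four tasks to the study or research group: building the 3D data set, assisting the surgeon in planning, supporting adherence, and conducting the questionnaires. Section {5d} gives the conduct of the trial and the data management to three physicians of that group. The overlap is therefore stated at group level. No sentence says that the individual who assisted a surgeon also hands that surgeon the form.

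**Step 2: is the direction in the text?** Section {11a} does not restrict assistance to the 3D arms. Section {12} requires a planned volume from all four modes, so the control arm has study-group contact as well. The only stated sign of unequal contact is the remark on first-time VR users in {11c}. A pull towards 3D is a reasonable inference, not a documented fact.

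**Step 3: how much could a shift matter?** The document gives no SD, no expected difference and no sample-size reasoning for SUS or NASA TLX, so there is no figure of its own to reproduce. What follows is an illustration.

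Inputs from the document:
- n = 25 per arm (section {14}).
- Two-sided local level of 0.017 (section {14}, stated there for the sample-size calculation).
- Independent t-test for group comparisons (section {20a}, stated after the continuous variables; its use for SUS is assumed).

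Inputs assumed:
- SUS SD of 12 to 20 points.
- A pure reporting shift b of 3 or 5 points in a 3D arm.
- No true difference.
- Independent ratings.

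Under a shift b, the two-sample t statistic has 2n − 2 = 48 degrees of freedom and noncentrality

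λ = b / (SD × √(2/n)), with √(2/25) = 0.283.

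The chance of a significant result is P(|T| > t_crit) for T ~ noncentral t(48, λ), with t_crit = 2.011 at 0.05 and 2.473 at 0.017. For b = 5 and SD = 15, λ = 5 / (15 × 0.283) = 1.18, which gives 21.1% at 0.05 and 10.7% at 0.017.

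| Shift b | SD | λ | Level 0.05 | Level 0.017 |
|---|---|---|---|---|
| 5 | 12 | 1.47 | 30.3% | 16.9% |
| 5 | 15 | 1.18 | 21.1% | 10.7% |
| 5 | 18 | 0.98 | 16.1% | 7.6% |
| 5 | 20 | 0.88 | 13.9% | 6.4% |
| 3 | 12 | 0.88 | 13.9% | 6.4% |
| 3 | 15 | 0.71 | 10.7% | 4.6% |
| 3 | 18 | 0.59 | 8.9% | 3.6% |
| 3 | 20 | 0.53 | 8.1% | 3.3% |

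These are rates for one 3D-versus-CT comparison. The nominal rates are 5% and 1.7%. Almost all of the rejections are in the direction of the shift: for b = 5 and SD = 20 at the 5% level, 13.7 of the 13.9 percentage points.

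**The case against.** **Self-completion may already be intended.** Section {11a} has the form given to the surgeon, section {19} speaks of paper, and section {18a} mentions interviews separately, for the teaching experience. Nothing says that researchers read out or discuss the items, and a condensed article may omit how forms are handed out. This stands as far as the sitting itself is concerned. It does not answer who conducts and receives the forms, because {18a} settles that in favour of the study group.

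**A reader might infer that the same researcher who helped a surgeon then questions that surgeon.** The text does not support this. It speaks of a member of the study group in one place and of the group's researchers in the other.

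**A reader might infer that the bias certainly favours 3D.** The document does not show this either. Control surgeons also need a planned volume and may receive the same assistance. The reconstruction program is commercial, and an outside company prints the models.

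**A reader might take SUS and NASA TLX to be the only secondary outcomes.** Section {12} reads that way, but the abstract lists secondary endpoints more broadly, including perioperative measures and teaching.

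**A courtesy effect common to the three 3D modes would largely cancel between them.** This is correct. The concern bears mainly on 3D versus CT, and on VR versus the other modes only if the extra VR support matters.

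**The size is assumed.** This also stands. The shift and SD are not from the document, and senior surgeons in one department are likely to rate several cases each, so the 25 ratings per arm may not be independent. The trial is described as exploratory, and the point concerns a secondary outcome.

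**Conclusion.** The concern holds as a risk of bias in a subjective secondary outcome. The document itself assigns the questionnaires to the group that builds the models and supports the surgeon, in an unblinded, single-department trial. The ratings are therefore open to courtesy bias, plausibly but not demonstrably towards the 3D arms, in the outcome used to judge feasibility.

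The size cannot be computed from the document. With an assumed 5-point SUS shift, SD 12 to 20, 25 independent ratings per arm and no true difference, false-positive rates are about 14% to 30% at the 5% level and 6% to 17% at 0.017. With a 3-point shift they are about 8% to 14% and 3% to 6%. These figures show only that modest shifts can matter at this sample size. No stated figure in the protocol is wrong on this point. The change is worth making mainly because it is so cheap.

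**What to change.** Amend sections {11a} and {18a} as follows:

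- The surgeon completes SUS and NASA TLX alone on paper after the operation, with no member of the study group present.
- Study-group members do not read out, explain or discuss items.
- The surgeon seals the form, marked only with the patient's serial number, and returns it to the study nurse, who passes it on unopened for data entry.

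**Cost.** A few sentences, envelopes and a small extra task for the nurse. No staff need be added, since section {5d} already provides a study nurse. Section {16b} describes the nurse who randomizes as independent and blinded about the trial; if this is the same person, the sealed return leaves that description intact. The Trial status section says recruitment had not begun, so at that stage the change could be made before any rating was collected.

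**What remains.** Surgeons still know which mode they used, and whoever enters the form can still link it to the case through the serial number. The change reduces the bias without removing it, so the report should state this limitation beside the usability results.

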### Plans to promote participant retention and complete follow-up {18b}

Since there is only a short follow-up period and no special action by the patients needed, there is no specific plan to facilitate the completion of follow-up. Data of patients who withdraw consent for the study, will not be used in analyses. If the surgeon in charge decides to take the patient out of their randomized group (i.e. in especially demanding cases) data will still be collected for an “as intended” analysis and in order to analyse all patients, who have been taken out of their randomized group.

### Data management {19}

The case report forms (CRF) with all patients’ characteristics, intraoperative and postoperative data and questionnaires are logged in paper format and stored in a locked closet in a locked room only accessibly for members of the research team. The CRF will be transferred to a local database for data analyzation using SPSS Statistics Version 27 (IBM, NY, USA). To promote data quality entries will be double-checked by a second researcher.

### Confidentiality {27}

The database, to which all of the CRF is transferred to, will only contain a unique number for each patient and no personal data. The unique number is logged in a separate database with personal data of each patient to facilitate follow-up, this database is only available to selected members of the study group. The paper forms of the CRF will be stored in a locked closet in a locked room, to which only the study group has access. The database containing the CRF will be stored locally and only be accessible to members of the research team as well.

### Plans for collection, laboratory evaluation and storage of biological specimens for genetic or molecular analysis in this trial/future sue {33}

Not applicable since there are no biological specimens collected.

## Statistical methods

### Statistical methods for primary and secondary outcomes {20a}

The primary analyses of the trial will adopt the per-protocol set (PPS), since there are only few dropouts to be expected. Patients withdrawing consent will not be included in analyses. Patients dropping out, due to a senior surgeons’ decision, will be analysed following the intention-to-treat (ITT) principle. The primary outcome, which is the quotient (RLV2-RLV1)/RLV1, will be analysed using the Wilcoxon Test. Continuous variables, as in the patients’ characteristics and perioperative and postoperative outcome, will be presented as mean ± standard deviation or median including interquartile range, depending on distribution. In order to compare the different study groups, an independent t-test will be applied. Variables with dichotomous values will be analysed using chi-square test.

### Interim analyses {21b}

There are no interim analyses at a fixed point in the study protocol planned. Since the intervention is not suspected to have an impact on patient safety, termination of the trial is not planned.

### Methods for additional analyses (e.g. subgroup analyses) {20b}

There are no additional analyses planned.

### Methods in analysis to handle protocol non-adherence and any statistical methods to handle missing data {20c}

Due to the short study period and the randomization not being affected by patients’ compliance or behaviour, missing data caused by non-adherence are not to be expected.

### Plans to give access to the full protocol, participant-level data and statistical code {31c}

Trial data will be available in the final publication. The full study protocol is accessible in the submitted manuscript.

## Oversight and monitoring

### Composition of the coordinating centre and trial steering committee {5d}

The trial steering committee will be composed of one principal investigator and two main investigators, in charge of administration and supervision of the study. Three physicians, who are part of the research group, will be responsible for conducting the trial in the coordinating centre, as well as data management. One study nurse will assist in the trial.

### Composition of the data monitoring committee, its role and reporting structure {21a}

There is no data monitoring committee planned to be in charge of the trial, since it is a monocentric study with low risk for patient safety.

### Adverse event reporting and harms {22}

Any adverse events (AE) or serious adverse events (SAE) will be monitored, recorded and in case of an SAE reported to the local ethical committee. In case of a suspected unexpected serious adverse reaction (SUSAR) report to the ethical committee will be made for reconsideration. Since the trial does not influence the method of operation and does not administer any study drugs, the occurrence of a SUSAR is deemed to be highly unlikely.

### Frequency and plans for auditing trial conduct {23}

A monthly supervision and discussion of study progress with the research group and at least one member of the steering committee is planned. Regular audits of the department include clinical trials.

### Plans for communicating important protocol amendments to relevant parties (e.g. trial participants, ethical committees9 {25}

All amendments and changes to the study protocol as well as changes in investigators will be reported to the local ethical committee right away. For trial specific communication with the local ethical committee, there is a two-step verification guarded online application available. Participants will be informed of changes by phone. Changes in time schedule that change the course of funding will be reported to the German Research Foundation.

### Dissemination plans {31a}

The results of this trial will be presented at relevant national and international conferences and the findings will be submitted for publication in peer-reviewed journals.

## Discussion

This study aims to explore the effect of different demonstration modes in planning of liver resections in order to provide surgeons with a tool to facilitate adequate planning in complex situations as well as to teach this important planning step to younger surgeons. The sample size for the study of 100 participants is expected to be attainable within two years in this high volume centre. However delayed inclusion can be seen in many clinical trials since the start of the COVID-19 pandemic, thus sufficient time to prolong recruiting, if necessary, is accounted for.

Group size of 25 patients in each group is sufficient for statistical analyses; however, it is possible that a skew between groups occurs due to very large tumours in need of extensive resection associated with higher perioperative risks. If applicable, a subgroup analysis with and without said outliers will be considered.

The trial is a first clinical test of resection planning in liver surgery in VR using a head-mounted display. Novel technologies usually raise interest at first but implementation in daily clinical use is a lengthy process, which is hardly predictable. Thus a lasting employment of VR using a head-mounted display for liver resection planning cannot be assumed. If implementation of this technology into daily practice is sustainably achieved and well accepted by users, expansion into different fields of operation planning is possible and desirable.

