### Objectives {7}

The objective of the trial is to compare the three demonstration modes of a 3D reconstruction of the liver, being 3D PDF, 3D print and 3D VR using a head-mounted display, to the current gold standard of a 2D CT scan displayed by a regular computer screen. The main end-point is the comparison of planned resection volume (RLV1) and actual resection volume (RLV2) measured by water displacement volumetry ((RLV2-RLV1)/RLV1). Furthermore, patients’ characteristics as well as intraoperative outcome and postoperative morbidity and mortality will be assessed to ensure comparability of study groups. The surgical team will be presented a questionnaire to usability and handling of the demonstration modes.

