## Interventions

### Explanation for the choice of comparators {6b}

Resection volume in liver surgery is a critical parameter correlating both to liver failure as well as postoperative morbidity. The presented trial aims to compare planned resection volume and actual resection volume throughout the aforementioned demonstrations modes to see which mode enables the most accurate prediction of resection volume. Furthermore, usability scores and handling of the different demonstration modes will be compared to determine, if one mode is preferable over the others. Patients’ characteristics as well as intraoperative outcome and postoperative morbidity and mortality are recorded for descriptive statistics and to unveil any imbalances of the study group. To compare patients’ general condition, the Charleson Comorbidity Index [17] is used; to assess postoperative complications, Dindo-Clavien Score and the comprehensive compication index are used.  (DOI: 10.1097/SLA.0000000000002902 [18]).

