### Concealment mechanism {16b}

Randomization will be performed by an independent study nurse, who is blinded about the trial, using opaque, sealed and unmarked envelopes being drawn from a box without putting them back. Each participant will be represented in the database by a serial number.

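### Skew from very large tumours is foreseen but met only with an undefined, optional outlier analysis that conflicts with section {20b}; the primary test does not adjust for tumour size

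*Protocol article*

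**What the plan says.** The Discussion of the protocol article accepts that 25 patients per group may not balance case mix: "it is possible that a skew between groups occurs due to very large tumours in need of extensive resection". Its only answer is "If applicable, a subgroup analysis with and without said outliers will be considered". It gives no tumour size or resection extent that makes a case an outlier, and no condition that sets the analysis off.

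The section on additional and subgroup analyses, {20b}, states "There are no additional analyses planned".

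For the primary comparison, section {20a} states "The primary outcome, which is the quotient (RLV2-RLV1)/RLV1, will be analysed using the Wilcoxon Test". It names no covariate. Section {12} acknowledges the heterogeneity: "Since liver resections can vary greatly in extent even in the chosen group of major resections". Section {6b} gives patient characteristics and the intra- and postoperative data a descriptive role; they "are recorded for descriptive statistics and to unveil any imbalances of the study group". Section {7} goes further: "intraoperative outcome and postoperative morbidity and mortality will be assessed to ensure comparability of study groups".

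The eligibility criteria {10} require a three-phase contrast-enhanced CT for every patient. Section {17a} plans no blinding. Section {16b} describes allocation "using opaque, sealed and unmarked envelopes being drawn from a box without putting them back" and mentions no stratification factor.

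**The concern.** Three things do not fit together.

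- **Two current statements conflict.** One section plans no additional analyses and another holds one in reserve. A reader of the results could not tell whether an analysis without the large tumours was planned.
- **The reserved analysis is open to the data.** Nobody is blinded and, under {18a}, the research group collects the data. The cut-off, the decision to run the analysis and the weight given to it could all be settled with groups and endpoint in view.
- **The foreseen factor is unused.** Tumour size is named as a likely cause of skew and can be read from a scan that exists before randomisation. Yet it enters neither the primary test nor the allocation.

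A related slip is that {7} and {6b} use intra- and postoperative results to judge whether the groups are comparable. These arise after the planning intervention and cannot show baseline balance.

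At stake are precision in arms of 25 and the credibility of the result if the two versions of the outlier analysis disagree.

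**Working it through.** The protocol gives no figure for the frequency of very large tumours, for the variance a covariate would explain, or for the target difference. Each is an assumption below.

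**1. Chance imbalance in large tumours.** Inputs: 25 per arm ({14}); prevalence 15% (assumed).

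- Expected number per arm: 25 × 0.15 = 3.75.
- SD of the difference between two arms: √(2 × 25 × 0.15 × 0.85) = 2.52.
- P(difference of 4 or more) for a given pair, exact from two Binomial(25, 0.15) counts: 0.16.
- P(largest minus smallest of four arms is 4 or more), simulated: about 0.50.

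With a fixed number of large tumours among 100 patients and four arms of exactly 25:

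| Large tumours per 100 (assumed) | Given pair differs by ≥4 | Largest v smallest arm differs by ≥4 |
|---|---|---|
| 8 | 6% | 26% |
| 12 | 13% | 43% |
| 20 | 22% | 61% |

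The pair figure is the relevant one for each 3D mode against CT. The four-arm range is larger because it picks the two most extreme arms.

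**2. Choosing between the two results.** Wilcoxon rank-sum test under no true difference, 25 per arm, local level 0.017 ({14}), normal errors, 10% or 20% large tumours (assumed).

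- Full set only: error about 0.015 per comparison.
- Better of the results with and without outliers, fixed definition: 0.021 to 0.024.
- Best of five size cut-offs (dropping none, or the largest 5%, 10%, 15% or 20%): about 0.027.

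These are upper readings: they apply only if the more favourable result is the one relied on.

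**3. Gain from adjustment.** Relative efficiency is 1/(1 − R²).

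- R² = 0.1: 1/0.9 = 1.11, like 11% more patients.
- R² = 0.3: 1/0.7 = 1.43, like 43% more patients.

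In terms of power: the SDs in {14} are 20% (control) and 10% (3D), so the root-mean-square SD is √((0.20² + 0.10²)/2) = 0.158. No difference is stated, so n = 23 cannot be reproduced from the protocol's inputs; it corresponds to a difference of about 15.6 points. Assuming 15 points, a two-sided t test at 0.017 with 25 per arm gives:

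| R² (assumed) | Power |
|---|---|
| 0 | 81% |
| 0.1 | 85% |
| 0.2 | 89% |
| 0.3 | 93% |

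**4. Which covariate is usable.** Tumour size on the eligibility CT precedes allocation. Planned resection volume (RLV1) does not: under {11a} and the participant timeline {13} it is obtained after allocation, with the allocated display mode, so it is part of what the intervention may change.

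**5. Whether blocking would help.** Simulating permuted blocks of 4 or 8 without strata, with 15% large tumours, leaves the four-arm probability at about 0.49 to 0.50. Blocks balance arms over time, not by tumour size.

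**The case against.** The other side has several good points.

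- **The full analysis stays.** The Discussion speaks of results both with and without these cases, and says so before recruitment. A reader might infer that the plan is to delete outliers from the primary analysis after the fact. The text does not support that. It describes an underspecified sensitivity analysis, and it identifies the cases by tumour and extent of resection, not by their endpoint value.
- **The unadjusted test is valid.** Chance imbalance under randomisation costs precision and does not bias the comparison. The endpoint is already relative to planned volume, a rank test resists extreme values, and {8} calls the trial exploratory.
- **The allocation is not shown to be defective.** A reader might infer that the envelope draw is unrestricted or that a redraw would go unnoticed. If the box holds equal numbers per arm, drawing without replacement fixes the arm sizes. An independent nurse draws, and patients are reported by unique serial number under {16c}. The article does not state the box contents or the logging, and it may leave them to the full protocol.
- **Covariates are often left to an analysis plan**, which is not shown.

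The first three points limit the finding and are accepted. The last stands only in part. An unseen plan cannot remove a contradiction inside the protocol, and {20a} does fix a particular unadjusted test. On comparability, {12} gives the later measures a descriptive purpose and no planned analysis conditions on them, so that slip is one of wording and interpretation.

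**Conclusion.** The point holds in moderate form. Sections {20b} and the Discussion contradict each other. The reserved analysis lacks a definition and a trigger in an unblinded trial. The primary test ignores a factor that the protocol itself expects to matter and that is available before randomisation.

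The benefit of repair is precision and protection from selective emphasis. It is not the removal of a systematic bias, since the documents show none. At an assumed prevalence of 15%, a given pair of arms differs by four or more large-tumour patients in about 16% of trials (about 50% for largest against smallest of four arms). The precision gain of 11% to 43% rests on an assumed R² of 0.1 to 0.3. It could be smaller, because the endpoint is already scaled by planned volume. The power figures also assume a 15-point difference and a t test, not the Wilcoxon test.

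**What to change.** 1. **In {20a}**, prespecify a comparison of the primary endpoint, on all analysed patients, adjusted for tumour size or volume on the pre-randomisation CT. Rank analysis of covariance on the protocol's own quotient would do this without changing the endpoint. Do not adjust for RLV1. State how tumour size is measured, including with several lesions, and record it before the envelope is drawn. Keep the unadjusted Wilcoxon test as a sensitivity analysis.
2. **Reconcile {20b} and the Discussion.** Either drop the outlier analysis, or list it in {20b} as a sensitivity analysis with a tumour-size cut-off on the pre-randomisation CT fixed in advance, always reported beside the full result.
3. **In {7} and {6b}**, judge comparability on baseline variables only and treat intra- and postoperative measures as outcomes.
4. **Optional:** a numbered allocation list in permuted blocks would improve balance over time, which is relevant because {11c} expects the technical support needed to fall during the study. It would not address tumour-size imbalance; adjustment, or stratification on tumour size, does.

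Items 1 to 3 cost a few sentences and one extra baseline measurement from an existing scan. The Trial status section says recruitment had not started at this version. Item 4 would cost one randomisation list.
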